#### Control strategy

BCM will not be used; physicians will estimate dry-weight from intake/output records, daily weight, clinical signs, and routine laboratory data to guide diuretic titration, and discharge timing will be determined at the clinician's discretion.

To minimize contamination between study groups, BCM measurements will be performed exclusively in the intervention group by independent research personnel who are not involved in routine clinical care. Participants in the control group do not undergo BCM measurement at any time during hospitalization. BCM results will not be entered into the electronic medical record and will not accessible to treating physicians caring for control-group participants.

#### Concomitant therapy

Management will adhere to international heart-failure guidelines. All participants will receive standardized education on sodium and fluid restriction, daily weight monitoring, and physical activity. Patients with HFrEF will be started as early as possible on quadruple goal-directed therapy with Angiotensin-Converting Enzyme Inhibitor/Angiotensin II Receptor Antagonist/Angiotensin Receptor-Neprilysin Inhibitor (ACEI/ARB/ARNI), Beta blockers, Mineralocorticoid Receptor Antagonist (MRA), and Sodium-Glucose Co-Transporter 2 Inhibitors (SGLT2i); vericiguat will be added when indicated unless contraindicated or not tolerated. Drugs will be initiated at evidence-based doses, uptitrated in rapid succession to target or maximum tolerated levels, prioritizing simultaneous introduction of agents with complementary mechanisms.

### Study outcomes and measurement

The primary outcome will be assessed at three predefined time points: 2 weeks, 4 weeks, and 12 weeks after discharge. Secondary clinical endpoints will be evaluated at the same time points as the primary outcome. Patient-reported quality of life measures will be assessed during hospitalization, at discharge, and at 12 weeks post-discharge. Additionally, assessments of symptom relief and safety monitoring will be conducted during the hospital stay (as detailed in Table 2).

**Table 2 T2:** Summarizes the timing of enrollment, interventions, and outcome assessments.

Visit ID	V1	V2	V3	V4	V5	V6
Case Report Form (CRF)	A	B		C	D	E
	Screening	Baseline/Randomization	Discharge	Follow-up 1	Follow-up 2	End-of-Study Visit
Time from Randomization	-1-0 week	-1-0 week	0 week	2 week	4 week	12 week
Assessment Window	–	–		±3 days	±3 days	±3 days
Informed Consent	X					
Demographic Data		X				
Personal History		X				
Physical Examination		X				
Comorbidities		X				
Laboratory Tests		X				X
Concomitant Medications		X		X	X	X
Event Adjudication				X	X	X
Heart Failure Symptom Assessment (KCCQ/VAS)		X	X			X (KCCQ)
Bioelectrical Impedance Measurement		X (Daily during hospitalization, intervention group)				

The primary outcome of this study is the composite endpoint of heart failure rehospitalization and all-cause death within 3 months after discharge; the secondary outcomes include rehospitalization for heart failure within 3 months after discharge, cardiovascular death within 3 months after discharge, all-cause death within 3 months after discharge, the change of Kansas City Cardiomyopathy Questionnaire (KCCQ) quality of life score from baseline to discharge and 3 months after discharge, the dose of diuretics used during hospitalization and dyspnea and changes in overall condition at 72 h after admission (VAS scale); the safety endpoints include the incidence of acute kidney injury and hypotension during hospitalization, the incidence of electrolyte imbalance during hospitalization and follow-up period.

The time origin for the primary endpoint is defined as the date of hospital discharge. Participants will be followed for 90 days after discharge.

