#### Endpoint definitions

Heart-failure rehospitalization is defined as an unplanned hospital admission lasting ≥24 h with a primary diagnosis of heart failure, accompanied by worsening signs/symptoms of congestion and requiring intensification of HF therapy (e.g., intravenous loop diuretics and/or vasoactive therapy). Planned admissions for elective procedures without clinical deterioration are not counted as endpoint events. All-cause death is defined as death from any cause occurring within 90 days after discharge.

Hypotension is defined as a systolic blood pressure <85 mmHg during hospitalization requiring reduction in diuretic therapy or initiation of vasopressor support.

Acute kidney injury (AKI) is defined as the occurrence of any one of the following: 1) Serum creatinine increases by ≥0.3 mg/dl (≥26.5 μmol/L) within 48 h; 2) Creatinine rises to >1.5 times baseline, indicating known or presumed renal dysfunction occurring within 7 days; 3) Urine output <0.5 ml/(kg·h) for at least 6 consecutive hours.

Electrolyte disturbances: 1) Hyperkalemia is defined as any serum potassium level >5.5 mmol/L observed during hospitalization or follow-up. 2) Hypokalemia is defined as any serum potassium level <3.5 mmol/L observed during hospitalization or follow-up. 3) Hyponatremia is defined as any serum sodium level <130 mmol/L observed during hospitalization or follow-up. Hypernatremia is defined as any serum sodium level >150 mmol/L observed during hospitalization or follow-up.

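### In-hospital safety monitoring is said to be set out in Table 2, but Table 2 does not contain it, so AKI, electrolyte and hypotension events may be ascertained unequally in this open-label trial

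*Protocol article*

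**What the plan says.** **Where the monitoring is said to be scheduled.** Under Study outcomes and measurement, the article states that "assessments of symptom relief and safety monitoring will be conducted during the hospital stay (as detailed in Table 2").

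**What Table 2 shows.** The row "Laboratory Tests" is marked at V2 (baseline/randomization) and V6 (12 weeks) and nowhere else. Physical examination is marked at baseline only. No row covers blood pressure, urine output or adverse events. The discharge column (V3) carries only the symptom and quality-of-life scales. The one daily in-hospital item is bioimpedance, "X (Daily during hospitalization, intervention group").

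**What has to be measured.** The same section says that "the safety endpoints include the incidence of acute kidney injury and hypotension during hospitalization, the incidence of electrolyte imbalance during hospitalization and follow-up period". Under Endpoint definitions, AKI is any one of three criteria: "Serum creatinine increases by ≥0.3 mg/dl (≥26.5 μmol/L) within 48 h"; "Creatinine rises to >1.5 times baseline, indicating known or presumed renal dysfunction occurring within 7 days"; or low urine output for at least 6 consecutive hours. Each electrolyte disturbance is any value beyond a limit, seen in hospital or in follow-up. "Hypotension is defined as a systolic blood pressure <85 mmHg during hospitalization requiring reduction in diuretic therapy or initiation of vasopressor support".

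**Who acts, and under which rules.** Strengths and limitations says that the clinical team cannot be blinded. The Intervention strategy section prescribes diuretic changes by OH value and lists hypotension, worsening renal function and electrolyte abnormalities as triggers for de-escalation. The Control strategy section leaves titration to the physician, who uses routine laboratory data among other things. It states no testing frequency and no trigger list.

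**The concern.** The text sends the reader to a schedule that does not contain what it is said to contain, and the safety endpoints cannot be derived from the assessments that the schedule does list.

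The missing data would have to come from routine care ordered by clinicians who know the allocation. That matters for three reasons.

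- An endpoint met by any abnormal value becomes more frequent as more samples are taken, even if the patients are no sicker.
- A creatinine rise within 48 h can be seen only if samples are close enough together.
- A low pressure becomes a hypotension event only if it requires a diuretic reduction or a vasopressor. Explicit de-escalation triggers are written under one arm's strategy only.

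Over-diuresis is the harm that the introduction sets against the hoped-for benefit, and the article says the trial will validate safety as well as efficacy. If ascertainment were unequal, the χ² or Fisher comparison would mix true harm with intensity of observation. It could then show harm that is not there or hide harm that is. The IDMC is to watch the same signals.

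**Working it through.** The plan gives no figure to reproduce here, so the main check sets each endpoint beside the printed schedule.

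| Endpoint (Endpoint definitions) | Data needed | Scheduled in Table 2 during the stay |
|---|---|---|
| AKI, criterion 1 | serial creatinine within 48 h | none after baseline |
| AKI, criterion 2 | creatinine within 7 days, against baseline | baseline value only |
| AKI, criterion 3 | urine output over 6 h | no row |
| Electrolyte disturbance | potassium, sodium | baseline only (one follow-up test, week 12) |
| Hypotension | systolic pressure and the clinician's response | no row |

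No in-hospital safety endpoint can be assessed from Table 2 as printed.

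**Does blinded adjudication repair this?** No. Event ascertainment and adjudication has the committee review suspected events, and a value never sampled raises no suspicion. The Blinding section describes its task as primary and secondary endpoint events, while safety endpoints are listed separately.

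**Would unequal testing matter? Illustration 1: number of samples.** Assume each potassium test has probability p of being abnormal, independently between tests. The chance of at least one abnormal value in k tests is 1 − (1 − p)^k. Neither p nor k is in the documents.

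| p (assumed) | k = 3 | k = 5 | k = 7 | 3→5 | 5→7 |
|---|---|---|---|---|---|
| 2% | 5.9% | 9.6% | 13.2% | 3.7 points | 3.6 points |
| 5% | 14.3% | 22.6% | 30.2% | 8.4 points | 7.5 points |
| 10% | 27.1% | 41.0% | 52.2% | 13.9 points | 11.2 points |

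For example, at p = 5%: 1 − 0.95³ = 0.143 and 1 − 0.95⁵ = 0.226. Repeated values in one patient are correlated, which shrinks the excess. With perfect correlation it is zero. Two extra tests per patient in one arm would therefore add between 0 and roughly 4, 8 or 14 points, depending on p and on the correlation.

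**Illustration 2: unequal detection.** Take n = 269 per arm (Sample size section), the same true rate t in both arms, detection of 90% in one arm, and detection d of 80%, 70% or 60% in the other. Observed rates are x = 0.9t and y = d·t, with mean p̄. The observed risk ratio is 0.9/d: 1.13, 1.29 or 1.50. By the normal approximation, the chance that a two-sided 5% test shows a significant excess in the more-tested arm is

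Φ{ [x − y − 1.96·√(2p̄(1 − p̄)/n)] / √([x(1 − x) + y(1 − y)]/n) }.

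For t = 20% and d = 60%: x = 0.18, y = 0.12, p̄ = 0.15. The numerator is 0.06 − 1.96 × 0.0308 = −0.0003 and the denominator is 0.0307, which gives 0.496.

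| True rate | d = 90% | d = 80% | d = 70% | d = 60% |
|---|---|---|---|---|
| 10% | 2.5% | 6.1% | 13.4% | 26.1% |
| 20% | 2.5% | 9.0% | 24.3% | 49.6% |
| 30% | 2.5% | 12.3% | 37.0% | 70.6% |

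**Illustration 3: sampling interval.** An abnormality lasting 24 h, starting at a random time, is caught with probability min(1, 24/T) when blood is taken every T hours: 1.0 at 24 h, 0.5 at 48 h, 0.33 at 72 h. Intervals that ordinary care could produce are enough to create detection gaps of the size assumed above.

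These figures show what unequal testing would do. They are not evidence that testing is unequal.

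**The case against.** **Condensation.** A journal article may leave a sampling timetable to the full protocol. Table 2 has no column between baseline and discharge, and it also omits the 72 h VAS assessment named in the text, so it reads as a visit summary. This would excuse silence. It does not excuse a cross-reference that tells the reader the detail is in the table.

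**No stated difference between arms.** A reader might infer that safety is in fact ascertained differently by arm, with more testing under the BIA strategy. The documents do not support that. Testing frequency is open in both arms, potential endpoint events are sought in the same hospital records, and control physicians also titrate on routine laboratory data. This objection stands in full: the arm difference is a risk, not a described feature.

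**Hypotension.** A reader might also infer that only the intervention arm can generate diuretic-reduction events. That goes too far. Control clinicians can reduce diuretics too, and the pressure threshold and the vasopressor route are common to both arms. A reduction made because OH is low is not one required by hypotension. Asking for a clinical consequence is a legitimate definition. What remains is that the consequence is decided by unblinded staff, with written triggers under one strategy only.

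**Status of the comparison.** Safety outcomes carry no confirmatory claim and are to be read with caution. That lowers the stakes, but caution in interpretation cannot recover values that were never measured.

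**Conclusion.** The point holds as an internal mismatch with a plausible consequence for bias. Study outcomes and measurement, Table 2 and Endpoint definitions do not fit together: the in-hospital safety endpoints rest on unscheduled tests and, for hypotension, on an action by unblinded clinicians. Ascertainment may therefore differ by arm. Whether it does, by how much and in which direction cannot be read from the documents.

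No single magnitude is justified. With equal detection the false-excess probability stays at 2.5%. With assumed detection of 90% against 60–80% it runs from 6% to 71% over true rates of 10–30%. The rates, the detection probabilities and the use of all 269 randomized per arm are assumptions. The primary endpoint is not affected. The matter should be corrected because it concerns the credibility of the safety comparison.

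**What to change.** 1. Reconcile the three places by adding to Table 2 one in-hospital assessment schedule, identical in both arms and including discharge, for creatinine, potassium, sodium, blood pressure and urine output. The intervals should allow the stated 48 h, 7-day and 6 h AKI criteria to be assessed.
2. Report the number of creatinine, potassium and sodium tests per patient by arm.
3. Keep all observed values in the main safety comparison and add a sensitivity analysis limited to scheduled samples. Restricting the main analysis to scheduled samples could miss real abnormalities between draws.
4. Keep the action-based hypotension endpoint, and report beside it the count of patients with systolic pressure below 85 mmHg alone, in both arms.

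These are changes of measurement and reporting; none alters treatment. The cost is an amendment during ongoing recruitment with ethics approval, some extra data entry, and possibly a few added samples in a population whose routine laboratory data are already used for titration. Participants enrolled before the change will have only routine-care data, so the sensitivity analysis should state how they are handled.

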## Introduction

Acute heart failure (AHF) is a clinical syndrome with rapid onset or sudden worsening of heart failure symptoms and signs, triggered by diverse etiologies. It is characterized by elevated plasma natriuretic peptides and often follows a life-threatening course that requires prompt medical intervention, frequently necessitating emergency hospitalization. Acute decompensation of chronic heart failure represents the predominant AHF phenotype, accounting for approximately 70%–80% of all AHF admissions, and is associated with poor prognosis. Registry data indicate that in-hospital mortality for AHF is approximately 12%, while the incidence of death or heart failure rehospitalization reaches 30%–45% within 90 days and 67% within one year (1). This high rate of readmissions places a substantial burden on global healthcare resources and leads to critical shortages in hospital bed capacity. Consequently, reducing potentially preventable readmissions has become a key priority for public health policy and hospital quality improvement programs worldwide.

This excess risk has been attributed to inadequate diuresis during index admission; over 50%–70% of patients are discharged with residual fluid overload (2–4). Conversely, intensified inpatient diuretic regimens attenuate congestion at discharge and improve post-discharge outcomes (3). Nevertheless, diuretic use and dose titration in AHF remain a double-edged sword. Early, aggressive diuresis rapidly relieves symptoms, shortens length of stay, and may reduce mortality (5). Conversely, the absence of precise guidance predisposes to over-diuresis, precipitating electrolyte disturbances, hypotension, and worsening renal function with resultant clinical deterioration (6, 7).

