### Statistical analysis

Analyses will be performed with SPSS 26.0 (SPSS Inc., Chicago, IL) and R 4.2.1 (R Foundation, Vienna). All analyses will follow the intention-to-treat principle, with participants analyzed according to the randomized assignment. Baseline characteristics will be summarized using mean (SD) or median (IQR) for continuous variables and counts (%) for categorical variables.

The primary endpoint (time to first occurrence of heart-failure rehospitalization or all-cause death within 3 months) will be analyzed using Kaplan–Meier methods and compared between groups using the log-rank test. Treatment effect will be estimated using Cox proportional-hazards models, reporting hazard ratios (HRs) with 95% confidence intervals. The proportional-hazards assumption will be assessed using Schoenfeld residuals. A prespecified adjusted Cox model will include clinically relevant baseline covariates (e.g., age, sex, BMI, LVEF, NYHA class, baseline NT-proBNP). Baseline diuretic dose (expressed as furosemide-equivalent dose) will be compared between groups and included as a covariate in adjusted analyses if clinically relevant imbalance is observed.

For time to first heart-failure rehospitalization, death will be treated as a competing event; Fine–Gray subdistribution hazard models will be used as a supportive analysis. Cardiovascular and all-cause mortality will be analyzed using KM/log-rank and Cox models as appropriate.

The total number of heart-failure rehospitalizations within 3 months will be analyzed using a negative binomial regression model (offset by follow-up time), reporting incidence rate ratios (IRRs) with 95% CIs. As a sensitivity analysis, a recurrent-event time-to-event model (e.g., Andersen–Gill) may be applied. Deaths occurring during the index hospitalization will be recorded as safety outcomes but will not be included in the primary time-to-event analysis, which focused on post-discharge events.

Changes in weight, NT-proBNP, and KCCQ scores over time will be evaluated using linear mixed-effects models with random participant intercepts, incorporating all available repeated measurements.

Safety endpoints (acute kidney injury, hypotension, electrolyte imbalance) will be summarized as counts (%) and compared using *χ*² or Fisher's exact tests.

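### AKI and hypotension are counted over a hospital stay whose length the strategy may change, and are compared only as crude percentages; diuretic dose shares the problem if it is a total

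*Protocol article*

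**What the plan says.** Under Study outcomes and measurement, the secondary outcomes include "the dose of diuretics used during hospitalization". No unit is given there, nor whether this is a total or a daily mean. The safety endpoints are "the incidence of acute kidney injury and hypotension during hospitalization" and "the incidence of electrolyte imbalance during hospitalization and follow-up period".

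Endpoint definitions again ties hypotension to the stay: "systolic blood pressure <85 mmHg during hospitalization requiring reduction in diuretic therapy or initiation of vasopressor support". The first AKI criterion is "Serum creatinine increases by ≥0.3 mg/dl (≥26.5 μmol/L) within 48 h". That limit, like the 7-day limit in the second criterion, describes how fast creatinine must rise. It does not cap the period over which AKI is counted.

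Statistical analysis says: "Safety endpoints (acute kidney injury, hypotension, electrolyte imbalance) will be summarized as counts" and percentages, compared by χ² or Fisher's exact test. No person-time, time-to-event or per-day measure is named for them. The paragraph after it classes all secondary endpoints as exploratory and asks for cautious interpretation of secondary and safety results.

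On what sets the length of the stay, Control strategy says "discharge timing will be determined at the" clinician's discretion. Intervention strategy lets the daily overhydration reading drive escalation, de-escalation and the move to oral dosing. The Introduction remarks, as background, "Early, aggressive diuresis rapidly relieves symptoms, shortens length of stay, and may reduce mortality". Length of stay is not among the outcomes in Study objectives or in Study outcomes and measurement.

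**The concern.** A proportion with any event during the stay depends on the risk per day and on the number of days watched. Here the second quantity is itself a result of care after randomisation, decided by clinicians who know the allocation. If one arm goes home earlier, it has fewer days in which AKI or hypotension can be seen and counted, even when daily risk is identical. A shorter stay could hide a higher daily risk; a longer one could produce a false signal.

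This matters because harm from over-diuresis is a central worry of the Introduction and Summary, AKI and hypotension are named as safety signals for the monitoring committee, and Strengths and limitations says the trial will validate safety as well as efficacy. With length of stay unreported, a reader could not tell which explanation applies.

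The article deals with unequal observation elsewhere: total heart-failure rehospitalisations are modelled with an offset for follow-up time, and the VAS outcome is fixed at 72 h. Neither device is applied to AKI, hypotension or diuretic dose.

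**Working it through.** The plan states no figure to reproduce, so the check is a reading of the window and the test, followed by an illustration.

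**Inputs.** From the article: 269 patients per arm (Sample size). Assumed, because the article gives none of them: a reference stay of 8 days, a stay of 5 to 11 days in the other arm, a reference incidence of 10%, 20% or 30%, and a daily hazard that is constant and the same in both arms.

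**Incidence.** With daily hazard λ and stay L, p = 1 − exp(−λL). For a reference incidence of 20%, λ = −ln(1 − 0.20)/8 = 0.02789 per day.

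- L = 6: 1 − exp(−0.02789 × 6) = 15.4%, risk ratio 0.77.
- L = 10: 1 − exp(−0.02789 × 10) = 24.3%, risk ratio 1.22.

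**Chance of a significant result from stay alone.** Normal approximation for two proportions, n = 269 per arm, two-sided 5%: Φ[(|p₁ − p₂| − 1.96·SE₀)/SE₁], with SE₀ pooled and SE₁ unpooled. For 15.4% against 20%: SE₀ = 0.0329, SE₁ = 0.0329, so Φ[(0.0459 − 0.0645)/0.0329] ≈ 29%.

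| Other arm's stay (reference 8 days) | Ref. 10%: incidence; chance | Ref. 20%: incidence; chance | Ref. 30%: incidence; chance |
|---|---|---|---|
| 5 days | 6.4%; 34% | 13.0%; 59% | 20.0%; 77% |
| 6 days | 7.6%; 16% | 15.4%; 29% | 23.5%; 40% |
| 7 days | 8.8%; 7% | 17.7%; 10% | 26.8%; 13% |
| 9 days | 11.2%; 7% | 22.2%; 9% | 33.1%; 12% |
| 10 days | 12.3%; 14% | 24.3%; 23% | 36.0%; 31% |
| 11 days | 13.5%; 24% | 26.4%; 42% | 38.8%; 57% |

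The chance would be 5% if the stays were equal. A one-day difference does little; two days or more matters.

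**Dose, if read as a total.** At the same mg per day the ratio of totals equals the ratio of stays: 6/8 = 0.75 and 10/8 = 1.25, with a range from 5/8 = 0.63 to 11/8 = 1.38. If it is a daily mean, this scaling disappears, although extra low-dose days late in a longer stay would still pull the mean down.

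**With a common window.** If everyone is observed for the first 72 h, equal hazard gives 1 − exp(−0.02789 × 3) = 8.0% in both arms, a risk ratio of 1.00 whatever the later stay. A window of seven days, or to discharge if earlier, does not achieve this. At 3% risk per day, stays of 5 and 7 days still give 1 − 0.97⁵ = 14.1% against 1 − 0.97⁷ = 19.2%.

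**The case against.** The strongest reply is that the trial compares management strategies, and the proportion of randomised patients with AKI or hypotension before discharge is a legitimate intention-to-treat summary. If a strategy shortens the stay and fewer events occur in hospital, that is part of its total effect. This stands, and is why the whole-stay incidence should be kept. It does not make that figure sufficient: an event that moves past discharge is not prevented, only uncounted.

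Other points limit the concern and also stand:

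- A reader might infer from the Introduction that the protocol expects a shorter stay in the intervention arm. It does not say so. The sentence is background on aggressive diuresis, whereas the tested strategy can step treatment up or down. No direction can be predicted.
- A reader might take the dose outcome to be cumulative. The article does not say so, and the choice of summary may be settled in the full protocol or analysis plan.
- Randomisation may come up to 24 h after admission, so a window starting at admission would include time before allocation. That time is balanced in expectation; it dilutes a contrast and does not bias it.
- Constant daily risk is a simplification. Dosing changes from day to day, and so may risk.
- Electrolyte imbalance also runs through follow-up, so it is less affected.

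**Conclusion.** The point holds for AKI and hypotension, where both the window and the test are stated and together leave the comparison open to differences in stay. It holds for diuretic dose only if that outcome is a total. On the assumptions above, a two-day difference in stay moves a 20% incidence to 15.4% or 24.3%, with a 29% or 23% chance of a nominally significant result at equal daily risk. These figures show what could happen. The article gives no evidence that stays will differ or by how much.

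A reader might go further and conclude that the trial's main result is compromised. It is not: the primary endpoint is timed from discharge over 90 days and does not use these windows. Secondary outcomes are already labelled exploratory, secondary and safety results are to be read cautiously, and deaths during the index admission are recorded as safety outcomes. This is an improvement worth considering and not a defect that must be cured before the trial can be interpreted.

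**What to change.** Keep the whole-stay incidence of AKI and hypotension as a descriptive, strategy-level summary, counted from randomisation, and add:

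1. AKI and hypotension over a short common window from randomisation in which nearly all patients are still in hospital (for example the first 72 h), without cutting off at discharge where data exist.
2. Time to first event, or events per patient-day in hospital, as support, with a note that its time base is itself determined after randomisation.
3. Furosemide-equivalent dose, the unit already used for baseline dose in Statistical analysis, over the same fixed window, together with mean daily dose. State which is the outcome.
4. Length of stay and in-hospital death by arm. Report them beside the safety results; adjusting for length of stay is not a clean remedy, because it arises after randomisation.

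The cost is a few sentences of endpoint wording and a little more analysis. Discharge date is already needed as the time origin of the primary endpoint. The sponsor should confirm that event onset dates and daily doses are captured in both arms: the article promises documentation of actual treatments within its description of the intervention, and Table 2 schedules laboratory tests only at baseline and week 12. The downside is that later in-hospital events enter only the whole-stay and rate summaries.

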#### Event ascertainment and adjudication

Potential endpoint events will be identified through 1) in-hospital electronic medical records and discharge databases, and 2) standardized follow-up contacts at 2, 4, and 12 weeks after discharge. For hospitalizations outside the study center, participants or family members will be asked to provide discharge summaries and key supporting documents (admission/discharge notes, medication records, imaging/laboratory reports). All suspected events will be adjudicated by an independent Clinical Events Committee blinded to treatment allocation and BCM data, using prespecified definitions. Disagreements will be resolved by consensus or a third adjudicator.

After investigators submit the relevant case-report documentation, independent, blinded medical adjudicators contracted for the study will determine 3-month cardiovascular mortality, all-cause mortality, number of heart-failure hospitalizations, time to first heart-failure admission, and any associated questionnaires.

The Kansas City Cardiomyopathy Questionnaire (KCCQ) will be administered at baseline by an independent, blinded assessor on site; at the 3-month follow-up, the same instrument will be completed via telephone by an independent, blinded assessor.

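### The post-discharge part of the electrolyte endpoint cannot be read as a 90-day incidence unless outpatient testing is frequent, and it is open to detection bias favouring the arm with fewer readmissions

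*Protocol article*

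**What the plan says.** All references are to the protocol article.

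- **Endpoint** (Study outcomes and measurement): "the incidence of electrolyte imbalance during hospitalization and follow-up period". Acute kidney injury and hypotension are limited to the hospital stay; only the electrolyte endpoint runs on into follow-up. On length: "Participants will be followed for 90 days after discharge".
- **Definition** (Endpoint definitions): "Hypokalemia is defined as any serum potassium level <3.5 mmol/L observed during hospitalization or follow-up". Hyperkalemia, hyponatremia and hypernatremia are worded the same way.
- **Schedule** (Table 2): the row "Laboratory Tests" is ticked at baseline and at the week-12 visit. It is blank at discharge, week 2 and week 4. The text above the table adds that "assessments of symptom relief and safety monitoring will be conducted during the hospital stay", which does not fit a safety endpoint that extends beyond the stay.
- **Sources** (Event ascertainment and adjudication): potential endpoint events come from "in-hospital electronic medical records and discharge databases" and from contacts at 2, 4 and 12 weeks. Laboratory reports from elsewhere are mentioned only for admissions: "For hospitalizations outside the study center, participants or family members will be asked to provide discharge summaries and key supporting documents".
- **Analysis** (Statistical analysis): "Safety endpoints (acute kidney injury, hypotension, electrolyte imbalance) will be summarized as counts (%) and compared using" chi-square or Fisher's exact tests. The section mentions no allowance for number of samples, time at risk or death for these endpoints.

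**The concern.** An event defined by any value observed exists only if blood is drawn. A participant who is never readmitted has one scheduled opportunity after discharge. A readmitted participant has that one (if alive) plus the inpatient samples, and under the article's own definition a heart-failure readmission involves intensified therapy such as intravenous loop diuretics.

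Two things are at stake. First, the post-discharge figure would be reported as an incidence over a period in which scheduled sampling covers one day. Second, the chance of detecting a safety event depends on readmission, a component of the primary endpoint. If the strategy reduces readmissions, its arm can show fewer electrolyte events with no true difference in electrolyte risk; if it increases them, the reverse holds. The article describes the trial as validating safety as well as efficacy, so the comparison will be read.

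**Working it through.** The article states no figure for this endpoint, so there is none to reproduce. The checks below ask what the stated schedule and test would yield.

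**Inputs from the article (Sample size):** 3-month composite rates of 24.9% (control) and 19.9% (intervention); 242 evaluable participants per arm.

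**Assumptions, not in the article, equal in both arms:** chance q of an abnormal value at the week-12 draw, 3% to 10%; chance r that a readmission shows an abnormal value, 10% to 50%; episode duration D, 3 to 30 days, with onset uniform over 90 days; in-hospital incidence h, 20% to 40%, independent of later events.

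**1. Coverage of one scheduled draw.** The share of episodes present on one given day is about D/90.

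| D (days) | Share caught |
|---|---|
| 3 | 3/90 = 3.3% |
| 7 | 7/90 = 7.8% |
| 14 | 14/90 = 15.6% |
| 30 | 30/90 = 33.3% |

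The scheduled draw alone misses more than half of the episodes whenever D is below 45 days.

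**2. False post-discharge difference under equal true risk.** Observed proportion P = q + (1 − q) × p × r, where p is the share readmitted, first set equal to the composite rate.

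- Central case, q = 5%, r = 30%: control 0.05 + 0.95 × 0.249 × 0.30 = 12.1%; intervention 0.05 + 0.95 × 0.199 × 0.30 = 10.7%. Difference 1.4 points, ratio 0.88.
- Furthest from 1, q = 3%, r = 50%: 15.1% against 12.7%. Difference 2.4 points, ratio 0.84.
- Nearest to 1, q = 10%, r = 10%: 12.2% against 11.8%. Difference 0.5 points, ratio 0.96.

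At 242 per arm, the chance that this artefact alone gives p < 0.05 in favour of the arm with fewer readmissions is 3.5% to 11.7%, against 2.5% with no artefact.

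**3. Deaths within the composite.** Step 2 treats every composite event as a readmission. With readmission at an assumed 20%, the central case depends on how the 5-point gap divides.

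- Readmission falls by the planned 20% relative, to 16%: 10.7% against 0.05 + 0.95 × 0.16 × 0.30 = 9.6%. The difference drops to 1.1 points and the ratio is 0.89.
- The whole 5-point gap is readmission, 20% against 15%: 10.7% against 9.3%. The difference stays at 1.4 points and the ratio is 0.87.

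Step 2 therefore bounds the absolute difference from above as long as deaths do not favour the control arm. The ratio is less firmly bounded.

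**4. Pooling with in-hospital events, as the endpoint is worded.** Pooled proportion = h + (1 − h) × P.

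- Central case, h = 20%: 0.20 + 0.80 × 0.121 = 29.7% against 0.20 + 0.80 × 0.107 = 28.5%, ratio 0.96.
- Central case, h = 40%: 0.40 + 0.60 × 0.121 = 47.3% against 0.40 + 0.60 × 0.107 = 46.4%, ratio 0.98.
- Over the corners of step 2 the pooled ratio runs from 0.94 (0.3012/0.3206; q = 3%, r = 50%, h = 20%) to 0.99 (0.4707/0.4734; q = 10%, r = 10%, h = 40%).

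**The case against.** The strongest reply is that Table 2 is not a full list of blood draws. It ticks no in-hospital test after baseline, yet the control strategy relies on routine laboratory data and acute kidney injury needs repeated creatinine. A blank at weeks 2 and 4 does not show that no blood is taken, the definition does not limit which samples count, and a journal article may leave such detail to the full protocol. This stands against any claim that samples come mainly from readmissions. It does not rescue the term incidence: the article states no route for collecting outpatient results, and irregular testing would still make detection depend on contact with care.

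A reader might go further and infer any of the following. The document does not support them.

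- *Most post-discharge events go unseen, or incidence is understated by some stated amount.* This needs episode durations and outpatient testing rates that the article does not give.
- *The arm with fewer readmissions looks safer by construction.* The bias needs a real readmission difference, is modest at the planned rates, and is diluted by in-hospital events. Deaths before week 12 remove draws and can push the other way.
- *Everyone is in the denominator and those who die unsampled count as event-free.* The article gives no denominator for these percentages. It also plans multiple imputation and sensitivity analyses for missing data.

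The article further says that safety estimates will be interpreted cautiously, without multiplicity adjustment. That limits the harm but does not correct the measure. Finally, a week-12 comparison among those sampled conditions on survival and attendance, and electrolyte events at readmission are real events. Both points stand, and they are why unscheduled values should still be reported.

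**Conclusion.** The point holds in limited form. The endpoint's period, its any-value definition, the single scheduled draw after discharge and the crude comparison do not fit together. Unless outpatient testing is frequent, the post-discharge part is not a 90-day incidence, and it is open to detection bias favouring the arm with fewer readmissions.

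The likely size is small to moderate: a false post-discharge difference of 0.5 to 2.4 percentage points (ratio about 0.84 to 0.96), which is the upper end because deaths are counted as readmissions. For the endpoint as pooled in the article the central case is about one point (ratio 0.96 to 0.98). These figures rest on the assumed detection probabilities and in-hospital incidence, and on no outpatient sampling beyond week 12. The endpoint should be corrected, but the primary analysis is not affected.

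**What to change.** Change the wording in Study outcomes and measurement, Endpoint definitions and Statistical analysis:

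1. Report in-hospital and post-discharge electrolyte disturbance as two separate outcomes.
2. Base the between-arm post-discharge comparison on the proportion abnormal at the scheduled week-12 draw among those sampled, with the numbers dead and the numbers unsampled shown by arm.
3. Report values found at readmission or at other unscheduled tests separately and descriptively, with the number of participants tested in each arm.
4. Do not call the result incidence over follow-up, and reconcile the sentence that places safety monitoring within the hospital stay.

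The week-12 samples are already scheduled, so no extra draws are needed. The costs are fewer counted events, a narrower claim (prevalence at week 12) and conditioning on being alive and sampled at that visit, which the counts in item 2 make visible but do not remove.
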